**Figure 1 f1:**
[figure not shown]
Protocol flow chart of the study. ABC, Autism Behavior Checklist; CARS, Child Autism Rating Scale; SDQ, Strengths and Difficulties Questionnaire; ADOS, Autism Diagnostic Observation Schedule; fNIRS, functional Near-Infrared Spectroscopy.

Participants were enlisted through advertisements in outpatient clinics, kindergartens, community bulletins, and social media platforms. Overall, 160 children aged 4–7 years who met the criteria for ASD, according to the criteria outlined in the Diagnostic and Statistical Manual of Mental Disorders, Fifth Edition (DSM-5), were enrolled. The formal diagnosis was determined using the gold standard instrument, the Autism Diagnostic Observation Schedule, Second Edition (ADOS-2), alongside clinical judgment by experienced psychologists. All participants were between the ages of 4 and 7 years old. Only children who satisfied the eligibility criteria (IQ score of at least 70) for the study were enrolled after completing the Wechsler Preschool and Primary Intelligence Scale (Chinese version) assessment, administered by a professional clinical psychologist. The randomization process was performed using SAS software (version 9.4, SAS Institute).

The primary objective of this study was to create and apply a behavioral training system using VR technology for preschool children with ASD. This system comprises a program utilizing VR technology, a real-time computer monitoring system, and a cloud-based management system. Participants in either the experimental or control group will receive 24 sessions of the intervention model (two sessions per week for 12 consecutive weeks). Participants will be assessed at six time points as follows: before the start of treatment; at 8, 12, and 16 weeks during the treatment period; and at 24 and 32 weeks following the completion of the intervention. The evaluation will follow the guidelines of good clinical practice. The assessment will include questionnaire scales completed by parents, observational scales administered by clinicians, and quantitative fNIRS to measure changes in hemoglobin (Hb) concentration at rest. These include indicators of training, behavioral symptoms, symptom severity, prosocial behaviors, and brain functioning.

The overall aim of this assessment is to compare and evaluate outcome differences between the two groups based on the intervention model results. Thus, we plan to assess the effectiveness of the behavioral training system using VR technology for preschool children with ASD. Concurrently, the intervention process will employ real-time data based on Continuous Performance Testing (CPT) technology to monitor changes in the training effects on the children.

### Sample size calculation

2.2

The sample size was determined based on the primary outcome measure and the scores from the ADOS scale. Previous studies reported an average ADOS-2 score of 16.9 ± 4.1 for children with ASD (25). In this study, we hypothesized a clinically meaningful difference of 2 points in the intervention group compared to the control group, indicating the efficacy of the VR-based intervention. The required sample size was calculated using the PASS 15.0 software, with the stipulation of α=0.05 and the test efficacy 1-β=0.8. This process yielded a sample size of 72 patients. Given a 10% loss of visits, the calculated sample size for each group was 80, with a total sample size of 160 cases.

### Eligibility criteria

2.3

Inclusion criteria:

Children diagnosed with ASD who met the DSM-5 diagnostic criteria and were further confirmed using the gold standard tool, the ADOS-2, with a total score >7 required for study inclusion;Age 4–7 years old;IQ>70 based on Wechsler Preschool and Elementary Intelligence Scale (Chinese version);Able to comprehend instructions with assistance from the researcher;No recent history of participating in other training programs.

Exclusion criteria:

Children with features of ASD but with neurometabolic epilepsy or epilepsy as the aetiology;Children with cerebral developmental disorders on cranial CT;Children with hearing abnormalities on audiometry;Children with Fragile X syndrome or other syndromes resulting from known genetic defects or inherited metabolic disorders;Children with other neurological or psychiatric diseases, including intellectual disability without ASD, schizophrenia, language disorders, and social communication disorder.

### Trial status

2.4

Currently, the trial status is recruiting. Inclusion of participants initiated on 24 December 2024. The anticipated end date is 30 September 2026.

### Randomization and blinding

2.5

Participants will be assigned randomly to either the experimental or control group in a 1:1 ratio, with randomization lists constructed by an independent statistician using SAS version 9.4 software. Group assignments were concealed using sequentially numbered, opaque, sealed envelopes prepared in advance. Upon enrollment, research staff opened the next envelope in the sequence to reveal the participant’s group assignment. Due to the nature of the intervention, blinding participants or therapists to group allocation was not feasible. However, to reduce assessment bias, all outcome evaluations will be conducted by independent assessors who are blinded to group assignments. To further ensure the reliability of outcome measurements, inter-rater reliability will be evaluated using intraclass correlation coefficients for clinician-administered observational tools such as the ADOS-2 and CARS. The results of the trial, including the patient’s identifying information and details of the intervention, will be de-identified. Final analyses will be performed by a statistician who remains blinded to group allocation.

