### Evaluation process

2.7

To ensure that participants meet the study criteria, the Wechsler Preschool and Primary Scale of Intelligence (Chinese revision) test was conducted before the study began to comprehensively assess the children’s overall intellectual ability. To evaluate how effective behavioral training using VR technology is in the rehabilitation of children with ASD, the following instruments will be administered: the parent-rated autism behavior checklist (ABC) to assess behavioral symptoms, Child Autism Rating Scale (CARS) to evaluate the severity of symptoms, Strengths and Difficulties Questionnaire (SDQ) to assess prosocial behavior, and Autism Diagnostic Observation Scale-2 (ADOS-2) to assess the child’s interactional behaviors. Brain function will further be assessed via the application of the fNIRS technique, which employs near-infrared light to gauge changes in cerebral blood flow. To ensure the authenticity and reliability of the data, parents received detailed instructions on how to complete the questionnaires, and all responses were reviewed for completeness at the time of collection. Any incomplete or questionable responses were verified and corrected in consultation with the parents. To enhance consistency and reduce variability, the same clinician and parent will complete the pre- and post-intervention assessments for each participant.

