#### Early family intervention

2.8.2

Early family intervention will adhere to the principles of child development. This intervention will entail a comprehensive assessment of each child and the formulation of an intervention program accordingly. The assessment will commence with an examination of each child’s neuropsychological development with the developmental characteristics of ASD. Subsequently, an assessment of the developmental level of children with ASD will be carried out across various domains. The assessment will further encompass an analysis of the family environment and all available resources. Based on the present analysis, an individualized education plan prioritizing social interaction as the core training content and utilizing games as the basic carrier will be formulated. Early family intervention will prioritize the family as the centre of intervention; as such, parents will be the primary implementers of the treatment, with therapists acting as supervisors. The therapist assumes the role of supervisor for the parents and oversees the implementation of the IEP at home. Parents will receive one hour of intervention training per week organized by the therapist. In addition, one hour of training per week will be conducted at home, in conjunction with the classroom video provided by the therapist. The intervention duration will be 12 weeks for each group. Weekly telephone and monthly outpatient follow-ups will be conducted to monitor the implementation of the parental intervention.

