In this study, we employed VR training as the primary intervention for the intervention group, and further introduced a two-player game mode to enhance social interaction opportunities. Additionally, the incorporation of pre- and post-intervention assessments is required to facilitate further to explore the effectiveness of interventions for children with ASD, as well as to extend the follow-up period to ascertain the sustainability of the observed effects. In the parent questionnaire, the SDQ will be used to assess the degree to which emotional problems have improved. However, this scale is inherently subjective when completed by parents alone. As such, the ADOS will be introduced by trained researchers to assess symptom improvement. This approach will help to standardize and codify behavioral observations using highly structured observations and tests, thereby enhancing the ability to detect core ASD deficits more effectively. Finally, fNIRS will be employed to assess brain function before and after the intervention, in order to evaluate the impact of VR-based training on brain plasticity, and to understand the neural mechanisms underlying behavioral improvement. To assess the sustainability of treatment effects, participants will complete follow-up evaluations at 24 and 32 weeks post-intervention. These extended assessments will help determine whether improvements in cognitive abilities, social communication, and daily living skills are maintained over time.

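### The statement that all outcomes are assessed blind is untrue of the ABC and SDQ, which parents complete knowing the arm

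*Protocol article*

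**What the plan says.** Section 2.5 (Randomization and blinding) concedes that "blinding participants or therapists to group allocation was not feasible". It then states that "all outcome evaluations will be conducted by independent assessors who are blinded to group assignments", and excepts no outcome.

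Other sections say who does the rating:

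- Section 2.1, in the text below Figure 1, lists among the assessments "questionnaire scales completed by parents, observational scales administered by clinicians", together with fNIRS.
- Section 2.7 (Evaluation process) includes "the parent-rated autism behavior checklist (ABC) to assess behavioral symptoms". The title of section 2.7.2 also calls this scale parent-rated.
- The Discussion says: "In the parent questionnaire, the SDQ will be used to assess the degree to which emotional problems have improved". It adds that "this scale is inherently subjective when completed by parents alone".

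On delivery, section 2.8.2 says of the family programme that "parents will be the primary implementers of the treatment". Section 2.9 gives that programme to both groups and the hospital VR sessions to the trial group only.

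On handling of parent forms, section 2.7 says: "Any incomplete or questionable responses were verified and corrected in consultation with the parents". Section 2.10 (Data management) requires corrections to records and related forms to be made as justified additions that are signed and dated.

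**The concern.** Section 2.7 names four behavioural scales for judging the training: ABC, CARS, SDQ and ADOS-2. For two of them the rater is the parent, who is neither independent of the family nor unaware of the arm. The control arm has no sham or attention-matched VR, so different expectations in the two arms are a plausible source of rating bias. Taken at its word, section 2.5 would let a favourable ABC or SDQ result be read as a blinded finding.

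A smaller matter lies in the query process. Section 2.7 does not define what makes an answer questionable, and it does not say whether the person raising the query knows the allocation.

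**Working it through.** The point turns on comparing statements. The only arithmetic is an illustration in step 4.

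**1. Who rates what**

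| Outcome | Rater or source | Section | Does the blinding sentence fit? |
|---|---|---|---|
| ADOS-2 | Clinician | 2.5 | Yes |
| CARS | Clinician | 2.5 | Yes |
| fNIRS | Instrument | 2.1, 2.7.6 | Feasible |
| ABC | Parent | 2.7, 2.7.2 | No |
| SDQ | Parent | Discussion | No |

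**2. Do parents know the arm?** Section 2.5 names only participants and therapists as not blindable, so this is an inference. It is a secure one. VR sessions take place at hospital and only in the trial group (section 2.9), twice a week for 12 weeks (section 2.8.1), which is 2 × 12 = 24 visits. The children are aged 4–7 and parents or guardians give consent (section 2.6).

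**3. What could bias the comparison?** Parents deliver the family programme in both arms, and a therapist accompanies the VR sessions (section 2.8.1). Delivery by parents is therefore common to both arms. What differs is the parent's knowledge of whether the child receives VR.

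**4. How sensitive would a parent-rated scale be?** The documents give no bias figure, so the bias b, in SD units, is assumed.

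- Evaluable number per arm: section 2.2 gives 72 before loss, and 72 / (1 − 0.10) = 80 per group, the stated figure. So n = 72 per arm.
- Test: two-sided 5%, critical value 1.96, no true effect, no multiplicity adjustment.
- Noncentrality: λ = b × √(n/2) = b × √36 = 6b.
- Rejection probability: Φ(λ − 1.96) + Φ(−λ − 1.96).

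| Assumed b (SD) | λ | Rejection, unadjusted 5% | Rejection, Bonferroni over four scales |
|---|---|---|---|
| 0.1 | 0.6 | 9% | 3% |
| 0.2 | 1.2 | 22% | 10% |
| 0.3 | 1.8 | 44% | 24% |

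The last column uses 0.05 / 4 = 0.0125 and a critical value of about 2.50. Section 3 plans Bonferroni correction where appropriate without naming the family, so the choice of four scales is also an assumption.

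**The case against.** The strongest reply is that nothing is hidden. The article calls the ABC parent-rated, says that parents complete questionnaires, and admits the subjectivity of the SDQ, which it gives as the reason for adding ADOS by trained researchers. The sentence after the blinding statement concerns clinician-administered tools, so the word *all* may be loose drafting. This stands as mitigation. It also means that no one can say the results would be reported as blinded, because that is a forecast. But the sentence is still a positive statement about design, and it is wrong for two scales.

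Several stronger readings are tempting, and the document does not support them:

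- **Parents bias the comparison because they deliver the treatment.** They deliver the family programme in both arms, so only knowledge of allocation can act between arms.
- **Parent answers are selectively corrected.** Section 2.7 describes a query to the respondent, worded alike for both arms. Section 2.10 already requires a justified, signed and dated addition. What remains is an undefined trigger and the unstated blinding of the person who queries. An article may leave such details to the full protocol, so this is only a secondary point.
- **The main efficacy result is compromised.** Section 2.2 sizes the trial on ADOS, which section 2.5 treats as clinician-administered and blinded.
- **CARS is also a parent questionnaire.** The Discussion groups it so when describing an earlier trial. For this trial, section 2.5 lists it as clinician-administered.

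**Conclusion.** The blinding statement in section 2.5 is wrong as written for the ABC and SDQ, two of the four behavioural scales, and should be corrected. This rests on the article's own account of who completes the scales and on the secure inference that parents know whether their child attends VR sessions. Choosing parent report for these scales is legitimate. The error is in describing them as blinded.

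The practical effect is to limit what an ABC or SDQ difference can support. ADOS-2 and CARS are outside the contradiction. The direction and size of any parent-rating bias are unknown. A reader might take the 9%, 22% and 44% as estimates of false-positive risk in this trial. They are not: they show only what assumed biases of 0.1, 0.2 and 0.3 SD would do at 72 per arm without multiplicity adjustment, and they fall if an adjustment is applied.

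**What to change.** 1. In section 2.5, limit the statement on blinded independent assessment to the clinician-administered and instrument-based outcomes: ADOS-2, CARS and fNIRS. Leaving out fNIRS would give up a commitment that is feasible.
2. State that ABC and SDQ are unblinded parent reports, to be interpreted as supportive and not sufficient alone for an efficacy claim.
3. As a smaller change, state in section 2.7 that queries on incomplete or questionable parent answers are raised by staff unaware of allocation, under the same preset rule in both arms, and that the original answer is kept in line with section 2.10.

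Verification should continue. Banning it would leave evident slips in the data and would treat forms differently before and after the change, since inclusion began on 24 December 2024. Answers that are kept should not be sent to multiple imputation, because section 3 plans that for missing outcome data and a retained answer is not missing.

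The cost is a few sentences and a short site instruction. Randomization, sample size, visits and instruments do not change. The query rule can govern only forms collected after it is adopted.

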### Ethics approval and informed consent

2.6

This randomized controlled trial was carried out under the guidance of Shanghai Children’s Hospital in China. Parents or guardians will be required to provide written informed consent before participating in the study. Participants will further be allowed sufficient opportunity and time to inquire and consult with their friends and family before making a final decision. Furthermore, parents and caregivers will ensure that their children’s treatment is not adversely affected, regardless of whether they participate in the experiment or not. It is also important to emphasize that participation in the experiment is entirely voluntary and that individuals maintain the right to drop out at any time. Further, all experimental steps will be preceded by obtaining written informed consent. The principal investigator or co-investigators must have an impartial witness present during the signing of informed consent forms. Due to the young age of the subjects (ranging from four to seven years old), it was deemed unnecessary to obtain personal consent from the patients themselves.

### Evaluation process

2.7

To ensure that participants meet the study criteria, the Wechsler Preschool and Primary Scale of Intelligence (Chinese revision) test was conducted before the study began to comprehensively assess the children’s overall intellectual ability. To evaluate how effective behavioral training using VR technology is in the rehabilitation of children with ASD, the following instruments will be administered: the parent-rated autism behavior checklist (ABC) to assess behavioral symptoms, Child Autism Rating Scale (CARS) to evaluate the severity of symptoms, Strengths and Difficulties Questionnaire (SDQ) to assess prosocial behavior, and Autism Diagnostic Observation Scale-2 (ADOS-2) to assess the child’s interactional behaviors. Brain function will further be assessed via the application of the fNIRS technique, which employs near-infrared light to gauge changes in cerebral blood flow. To ensure the authenticity and reliability of the data, parents received detailed instructions on how to complete the questionnaires, and all responses were reviewed for completeness at the time of collection. Any incomplete or questionable responses were verified and corrected in consultation with the parents. To enhance consistency and reduce variability, the same clinician and parent will complete the pre- and post-intervention assessments for each participant.

#### Wechsler Preschool and Primary Scale of Intelligence (Chinese version)

2.7.1

The WPPSI is a psychological tool used to assess the cognitive abilities of children aged 36 to 95 months. The WPPSI will primarily be used to establish a starting point for the children involved in the study (26). This test comprises 15 subtests which assess children’s overall cognitive functioning, including general knowledge, missing places, and vocabulary. This assessment includes the Verbal Comprehension Index (VCI), Visuospatial Index (VSI), Fluid Reasoning Index (FRI), Working Memory Index (WMI), and Processing Speed Index (PSI), which collectively assess intelligence (27).

#### Parent-rated Autism Behaviors Checklist

2.7.2

This scale assesses the behavioral status of children and comprises 57 items pertaining to the characteristics of children with ASD. These include five aspects: sensation, interaction, body and object use, language, and social life self-care. Each item receives a score ranging from 0 to 4 on a 5-point scale, yielding a total possible score of 158 points. A score of ≥62 points is sufficient for the diagnosis of ASD, with higher scores suggesting more severe associated behavioral symptoms (28).

#### Child Autism Rating Scale

2.7.3

This scale has previously been employed to evaluate symptoms of ASD in children diagnosed with ASD aged 2 years or older. This 15-item scale is designed to assess behaviors across 14 domains that are commonly impacted by severe issues in ASD, as well as an overall impression. Each item is scored on a 4-point scale. A total score below 30 indicates that the participant does not have ASD. Scores between 30 and 36 indicate mild to moderate ASD, while scores of 36 or higher indicate severe ASD (29).

#### Strengths and Difficulties Questionnaire

2.7.4

This scale is predominantly used to evaluate emotional and behavioral problems in children and adolescents. The scale comprises five subscales: emotional symptoms, conduct problems, hyperactivity and attention deficit, peer relationships, and prosocial behavior. The first four subscales comprise the Difficulties Questionnaire, which assesses negative emotions and behavioral problems. In contrast, the Pro-Social Behavior subscale serves as the Strengths Questionnaire, which reflects positive behaviors. A higher score on the Difficulties Questionnaire indicates a more severe problem, whereas a higher score on the Strengths Questionnaire indicates more positive behavior. This scale has previously been utilized to evaluate prosocial behavior in children with ASD (30).

#### Autism Diagnostic Observation Schedule, Second Edition

2.7.5

ADOS-2 is a semi-structured assessment tool designed to evaluate the interactive behavior of children. This scale comprises four modules, with module 2 focusing on children who have limited language abilities and are unable to communicate in an efficient and fluid manner, primarily within the context of preschool education. Each module comprises five items and assesses communication, social interaction, playing with objects using them imaginatively, as well as individual stereotypical and repetitive behaviors (31). Each item is rated on a scale from 0 to 2, where 0 represents typical performance and 2 indicates abnormality. Higher scores indicate more severe symptoms (32).

